## Methods

### Trial Design, Setting and Registration

This is a parallel, randomized, triple-blind, sham controlled clinical protocol in which a total of 90 drug-naïve, first-episode MDD outpatients (45 per arm) will be randomized to one of two groups: active bilateral tDCS over the DLPFC combined with CBT or sham tDCS combined with CBT (Figure 1).

**Figure 1 F1:**
[figure not shown]
Overview of the Study design (tDCS, transcranial Direct Current Stimulation; CBT, Cognitive Behavioral Therapy).

Patients will complete a 6-weeks treatment that involves 18 tDCS sessions (active or sham) and 12 CBT sessions. For the first 2 weeks of intervention, they will receive 10 daily sessions of tDCS (from Monday to Friday) and 4 sessions of CBT (combined at same time with tDCS for the first 30 min, on Monday and on Friday). They will then receive two booster sessions of tDCS combined with CBT will be on weeks 3, 4, 5, and 6 (Figure 2B).

**Figure 2 F2:**
[figure not shown]
Schematic representation of the main phases of the trial. **(A)** Shows the timeline of assessments. **(B)** Details how interventions sessions will be administered by week.

This study will then be organized in 3 distinct phases. Phase 1: Recruitment and baseline assessments; Phase 2: Intervention; Phase 3: Post-treatment assessment and 6-month follow-up (Figure 1). Once eligibility is determined and consent provided, patients will be randomly assigned to one of the two groups in a 1:1 allocation ratio, by the means of a list generated by an automatic web-based randomization program.

After an initial baseline assessment (visit 1) (for more details see task 1), patients will receive 10 consecutive sessions (in two weeks) of active or sham tDCS (2 mA, 30 min), and 6 sessions of CBT every other day (3 CBT sessions per week). Patients may fail 1 or 2 sessions of tDCS and/or CBT; and in that case, they will have the opportunity to receive the missing session (s) in the following week. The primary outcome will be assessed by week 2, using MADRS. Other assessments will be also performed by week 2, such as EEG, and other clinical measures (see Table 1). By week 4 and 6, patients will receive additional booster sessions of the same intervention (active or sham tDCS followed by CBT). Patients will perform the same assessments on week 6 (Figures 2A,B). tDCS sessions will follow the same design previously tested by two members of our group, that showed significant clinical effects of tDCS alone, and tDCS combined with sertraline in moderate to severe MDD (21).

**Table 1 T1:** Summary and timeline of assessments.

	**Consent and Screening**	**Assessment pre-intervention**	**EEG pre-intervention**	**Interventions Session and tDCS**	**Assessment 15 days**	**EEG 15 days**	**Interventions Session and tDCS**	**Assessment post-intervention**	**EEG post-intervention**	**Follow-ups**	
				***Daily Sessions***			***Bi-weekly sessions***			***15 day, 1, 2, 3, and 5 months***	
	**Email / Visit 1**	**Visit 1**	**Visit 2**	**Visit 3-12**	**Visit 13**		**Visit 14-21**	**Visit 22**		**Visit 24 – 27**	
***Approximate visit time***	***1 h 30 min***	***30 min***	***1 h***	***50 min***	***30 min***		***50 min***	***30 min***		***30 min***	
**PRESCREENING FOR ELIGIBILITY, CONSENTING, AND CLINICAL INTERVIEW**											
Pre-screening questionnaires (inclusion and exclusion criteria)	X										
Consent Informed (2 copies)	X										
Questionnaire eligibility for the study	X										
Questionnaire eligibility to tDCS	X										
Questionnaire eligibility to EEG	X										
Demographics and medical questionnaire		X									
The structured clinical interview for DSM-5 (SCID-V)		X									
**PRIMARY AND SECONDARY OUTCOME ASSESSMENTS**											
The satisfaction with life scale (SWL)		X			X			X		X	
The pittsburgh sleep quality index (PSQI)		X			X			X		X	
State-trait anxiety inventory (STAI-Y)		X			X			X		X	
Beck anxiety inventory (BAI)		X			X			X		X	
Beck's depression inventory (BDI)		X			X			X		X	
Montgomery-asberg depression rating scale (MADRS)		X			X			X		X	
Blinding questionnaire								X			
Visual analog scales (VAS)—pre and post				X			X				

Structured CBT sessions will follow the NICE guidelines from the National Institute for Health and Care Excellence (39). Patients will receive a total of 12 CBT sessions administered biweekly for 6 weeks. Mood, will be evaluated at the end of each week, as to perform the dose calculation (i.e., number of sessions) required to induce a clinical significant effect of at least 50% decrease in the MADRS scores.

In addition to the primary outcome measure (MADRS), secondary outcome measures will be clinical response as measured by scores on the 17-item Hamilton Depression Rating Scale, Beck Depression Inventory (BDI), Beck Anxiety Inventory (BAI), clinician-rated Clinical Global Impression–Severity of Illness scale, and quality of life (QoL). These scales will be used at baseline, week 2, 4, 6, and follow-ups (up to 6-month follow up).

Resting-state EGG assessments will be performed on baseline session, on weeks 2 and 6. These assessments will allow us to assess the neural effects of these interventions in the brain.

The Standard Protocol Items: recommendations for Interventional Trials (SPIRIT) statement were used as a framework for developing the study methodology for this trial (40, 41).

### Participants

A total of 90 drug-naïve, first-episode MDD outpatients (45 per arm) will be randomized to receive either CBT combined with active bilateral tDCS over the DLPFC or CBT combined with sham tDCS.

### Eligibility Criteria

Participants will be included in this study if they meet the following criteria: 1) Aged 18–75 years; 2) Unipolar, nonpsychotic MDD (DSM-V); 3) Score in the MADRS 7 and above (mild, moderate, and severe depression); 4) Low risk of suicide, as evaluated during the clinical interview and through the Scale for Suicidal Ideation [Mild to Moderate SIS; (42)]; and 5) Able to sign informed consent.

Potential participants meeting any of the following criteria will be excluded: 1) any contraindication to receive tDCS (such as metal in the head, implanted brain medical devices); 2) any significant or unstable neurologic or psychiatric disorder other than MDD, such as epilepsy, Parkinson's Disease, Dementias, eating disorders, OCD Spectrum disorders, among others); 3) history of substance abuse within the past 6-months, 4) Any personality disorders; or 5) any severe life-threatening disorders or concurrent medical condition likely to worsen patient's functional status in next 6-months such as; cancer, or severe heart, kidney, or liver diseases. Participants with reported high risk of suicide will be excluded from the study and will be recommended to receive support from an experience and licensed psychologist/psychiatrist. Information about local and national institutions that provide support to cope with suicidal behaviors and though will be provided.

A screening questionnaire that addresses the specific inclusion and exclusion criteria will be applied to each participant prior to the SCID-5 interview and will help to screen out participants. Diagnosis will be performed using the Structured Clinical Interview for DSM-5 (SCID-5) (43, 44), a widely used semi structured clinical interview designed to evaluate psychopathology, following the categories in the DSM 5 (Diagnostic and Statistical Manual of Mental Disorders, Fifth Edition) for the clinical use and clinical research. Potential participants will also answer the tDCS eligibility questionnaire and the SIS to evaluate the likelihood of suicide attempt. Patients with high likelihood of suicide attempt will be not included in our study and will be recommend for psychological and/or psychiatric intervention.

### Description of the Interventions

#### Cognitive-Behavioral Therapy (CBT)

CBT will be performed following the structure proposed by Beck et al. (17, 45). Each session will last 60 min and will be designed individually for each patient, according to the severity of Depression—including behavioral activation and problem-solving techniques. A licensed and trained practitioner will be responsible for facilitating the self-help programme and for reviewing progresses and outcomes during psychotherapy sessions. A senior clinical psychologist with extensive experience in CBT in patients with depression will supervise the clinical work. A clinical meeting will be hosted weekly in order to perform quality assurance of the therapeutic process.

#### Transcranial Direct Current Stimulation (tDCS)

tDCS will be delivered by an Eldith DC Stimulator Plus (Neuroconn, Germany), using 25 cm^2^ saline-soaked electrode sponges. Anode will be placed over the left (F3) and cathode over the right DLPFC (F4). For the active tDCS, participants will receive 2 mA (current density = 0.80 A/m^2^; with 15/15 s ramp/ramp down) for 30 min/d. For sham tDCS, patients will receive 15 s of 2 mA intensity, and 15/15 s ramp in and ramp down, with the same montage of electrodes; however, the device will be turned off after 45 s of active stimulation. Each tDCS session will last about 40 min: 30 min of stimulation and 10-min of set up. tDCS sessions will be performed by a research assistant, not involved in the CBT sessions.

### Description of the Assessments

These instruments will be used at baseline, after the first 2 weeks of intervention, at the end of the 5-weeks of biweekly sessions and follow-up visits (up to 2 months after the intervention period) as detailed in the table below. Please see Table 1 for the complete assessments timetable.

### Outcomes

#### Primary Outcome

For the depression assessment, we will use the Montgomery-Asberg Depression Scale (MADRS) as primary outcomes. Criteria for the use of this clinical scale will be the same as we previously used in Brunoni et al. (21). Secondary outcomes will include also the clinical response (categorical variable, defined as > 50% reduction of the baseline MADRS score), clinical remission (categorical variable, defined as a MADRS scores ≤ 10), and scores on the BDI.

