### Sample Size Calculation

For the sample size calculation, we assume an effect size(d) of 0.66 [upper limit for the 95% CI of the pooled effect size of tDCS on MDD (22) that for a two-side α of 0.05 and a power of 80%, requires a total of 76 patients (38 per group). We increased the sample size by 15% to 45 per group to account for unexpected factors. This sample size will be adequate to detect this magnitude of effect.

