#### Demographic and Clinical Assessments

*Demographics information:* We will record information about the demographic characteristics of the study population such as age, gender, race, level of education, and social status.

*Medication Use Log:* Medication use information will be obtained at enrollment and updated on a weekly basis, by means of a Medication Log. Participants will record their current medications and dosages weekly, until completion of the study. Medication diaries are commonly used to record changes in medication use during the study period. We will also use the Antidepressant History Treatment Form (ATHF) to assess treatment refractoriness.

*Montgomery-Asberg Depression Scale* (MADRS): For the depression improvement assessments, we will use the MADRS for the primary outcome. This is widely used scale for the measurement of severity of depressive symptoms in patients with MDD. The scale is divided into 10 items, each scored on a 0 to 6-point ordinal scale (54). The MADRS will be administered according to a structured interview procedure that has been empirically found to result in high inter-rater reliability scores.

*Beck Depression Inventory (BDI):* This self-report inventory consists of 21 multiple-choice questions and is a widely used method to classify depression severity (55). It assesses for the presence of several symptoms related to depression, such as irritability, hopelessness and decreased cognitive performance. Physical symptoms such as weight loss and fatigue are also included. The total time required to complete this inventory is 5 to 10 min.

*Quality of Life Assessment (Short version of SF-36):* The short version of the SF-36 health survey is used as a measurement of quality of life. It provides a profile of functional health and well-being scores. It is also used as a psychometrical index of physical and mental health (56).

*Satisfaction with Life (SWL)*—is a short and rapid 7-point Likert scale that measures life satisfaction in the perspective of subjective well-being. Scores in SWL have been positively correlated with measures of mental health and also predictive of future maladaptive behaviors such as suicide attempts (57, 58).

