Therefore, the results of this project will further provide important insights into the mechanisms underlying MDD. In sum, we will be able to study the mechanistic reason underlying differences between the add-on treatment group vs. CBT combined with sham tDCS. We chose a population that is not very well studied, namely patients drug-naïve, first-episode MDD with mild to moderate symptoms, because several studies failed to show the link between decreased left frontal activation and depression. By using resting state EEG, it will be possible to simultaneously understand the neural effects of the intervention, as well as potential response predictors for future trials.

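### The entry score (MADRS 7 and above) overlaps the definition of the secondary outcome remission (MADRS 10 or less), so a patient entering at 7 to 10 would count as remitted without improving

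*Protocol article*

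**What the plan says.** Under Eligibility Criteria, the protocol article includes patients with "Score in the MADRS 7 and above (mild, moderate, and severe depression", together with a diagnosis of unipolar, nonpsychotic MDD made by structured interview. The Discussion describes the population as "patients drug-naïve, first-episode MDD with mild to moderate symptoms".

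Under Outcomes, in the subsection headed Primary Outcome, the MADRS is the primary measure. The same paragraph then adds secondary outcomes, among them "clinical response (categorical variable, defined as > 50% reduction of the baseline MADRS score") and "clinical remission (categorical variable, defined as a MADRS scores ≤ 10"). Response is thus measured against the patient's own baseline, whereas remission is a fixed score with no baseline condition and no required change.

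On scoring, Demographic and Clinical Assessments says: "The scale is divided into 10 items, each scored on a 0 to 6-point ordinal scale". Totals are therefore whole numbers from 0 to 60.

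The article states no higher entry score and no restriction of the remission analysis to patients who start above 10.

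**The concern.** Remission should mark a patient who was ill at entry and is no longer so by the trial's own criterion. Here the lowest admissible entry score lies below the remission cut-off. A patient at 7, 8, 9 or 10 already satisfies the definition on the day of randomisation and cannot newly achieve it.

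At stake is how one secondary outcome can be read. Such patients add remitters to both arms whom treatment did not produce. The rate in each arm then partly reflects who was enrolled, and the difference between arms shrinks because these patients contribute little or nothing to it. Remission also becomes inconsistent with response, since a patient can remit without responding.

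**Working it through.** **1. The plan's own figure.** The article gives no sample size or power for remission. Its only calculation is for the primary outcome ("we assume an effect size(d) of 0.66", two-sided 0.05, 80% power). By the normal formula, 2 × (1.96 + 0.84)² / 0.66² ≈ 36, which rounds up to 37 per arm without intermediate rounding of the quantiles. The t-test version gives 37.02, hence 38 per arm as stated. Then 38 / 0.85 = 44.7, hence 45. The figure reproduces, and the remission cut-off does not enter it.

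**2. The overlap.** Entry scores run from 7 to 60 (Eligibility Criteria and the item scoring). Remission scores run from 0 to 10 (Outcomes). The scores common to both are 7, 8, 9 and 10.

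**3. Comparison with response.** A fall of more than 50% from 10 means a score below 5, and from 7 a score below 3.5. The same patients need no fall at all to be remitters.

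**4. How many patients.** The case mix is not given, so the share is shown for four assumed normal baseline distributions, truncated at 7, with continuity correction:

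q = [Φ((10.5 − m)/s) − Φ((6.5 − m)/s)] / [1 − Φ((6.5 − m)/s)]

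For mean 16 and SD 6: (0.1797 − 0.0567) / (1 − 0.0567) = 0.130.

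**5. Effect on the rates.** Let p be the remission rate in patients entering above 10, and r the proportion at 10 or less among those entering at 7 to 10, taken as equal in both arms. Then:

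- observed rate = (1 − q) × p + q × r
- observed difference = (1 − q) × true difference

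The dilution therefore depends on q alone. The inflation depends on q, p and r. The illustration assumes p = 30% (sham) and 50% (active), and r = 85%. None of these rates is in the document.

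| Assumed mean, SD | q | Of 90 | Sham | Active | Difference (points) |
|---|---|---|---|---|---|
| 24, 7 | 2.1% | 2 | 31% | 51% | 19.6 |
| 20, 7 | 6.2% | 6 | 33% | 52% | 18.8 |
| 16, 6 | 13.0% | 12 | 37% | 55% | 17.4 |
| 14, 5 | 18.8% | 17 | 40% | 57% | 16.2 |

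For the third row: sham 0.30 × 0.87 + 0.85 × 0.13 = 0.37; active 0.50 × 0.87 + 0.85 × 0.13 = 0.55 (0.5455); difference 0.20 × 0.87 = 0.174.

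**6. Cost of leaving these patients out of the remission analysis.** At q = 13%, about 45 × 0.87 = 39 per arm remain. Normal-approximation power is about 38% with 45 per arm (37% against 55%) and about 44% with 39 per arm (30% against 50%). On these assumptions the smaller set loses no power. The comparison is weakly powered either way, as expected for a secondary outcome on which the trial was not sized.

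**The case against.** The strongest reply is that this may hardly ever occur. Entry also requires MDD confirmed by structured interview, and few such patients may score 7 to 10. That stands as to number. A reader might infer that some patients will in fact be remitted at entry, but the document only permits this and gives no baseline distribution. The interview reduces the likelihood without excluding the case, and the criterion deliberately takes in mild depression.

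Second, only a secondary outcome is touched. That stands in full. Because the definition sits under a heading for the primary outcome, a reader might think the main result is affected. It is not: the primary analysis is a mixed-model ANOVA of MADRS scores.

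Third, a reader might infer that a chance imbalance of low scorers between arms would bias the comparison. The document does not support that. Under randomisation such imbalance is ordinary sampling variation, reflected in the confidence interval. The Statistical Analysis section also foresees severity as a covariate if the arms differ at baseline, though it says so for the MADRS analysis.

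Fourth, handling may lie elsewhere. The analysis plan is not shown, and the article says "Criteria for the use of this clinical scale will be the same as we previously used in" an earlier trial. This limits any claim that the matter is unhandled. It does not remove the conflict, because both cut-offs are fixed in this article and applying them as written gives the wrong count.

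**Conclusion.** The overlap is real and follows from the article's own figures: any patient entering at 7 to 10 meets remission at baseline and would be counted a remitter at any visit with a score of 10 or less. This inflates the remission rate in both arms and dilutes the arm difference in proportion to the share of such patients.

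The size is uncertain. Under the assumed distributions the share is about 2% to 19%, which turns a 20-point difference into 19.6 to 16.2 points. These figures rest on the assumed baseline means and SDs, the assumed 30% and 50% rates, and the assumption that low scorers stay at 10 or less equally often in both arms. The effect may be slight. The point is worth correcting because it is cheap to settle while the trial is recruiting, and because it makes the remission rates hard to interpret.

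**What to change.** Reconcile Eligibility Criteria with the remission definition under Outcomes. For the analysis, define the remission set as all randomised patients with baseline MADRS above 10, and include baseline MADRS as a covariate. Because the score is obtained before randomisation, the subset keeps the randomised comparison. The number excluded in each arm should be reported.

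Adding a baseline condition to the definition while keeping everyone in the denominator would not solve the problem. Patients entering at 7 to 10 would then be forced non-remitters. With the same inputs the rates would be 0.30 × 0.87 = 0.261 and 0.50 × 0.87 = 0.435, again a difference of 0.174.

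The cost is a change to outcome wording and analysis set, and a somewhat smaller denominator for one secondary outcome. The primary analysis and the sample size need no change on this account.

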#### Secondary Outcomes

Resting state EEG and task-elicited prefrontal EEG alpha asymmetry—Resting state EEG screening will be carried out before the intervention (baseline), and in the end of each week of intervention. Each screening will comprise a resting state EEG (3 min eyes open and 3 min eyes closed) and a task-related EEG data collection. The task-related screening will last about 3-min in an open-eyes active state. For this task, we will use a facial emotion task, with approach and avoidance facial expressions, similar to the task used by Stewart and colleagues

EEG will be acquired using 20 channel Starstim (Neuroelectrics, Barcelona, Spain), following the 10/20 system, in a continuous mode at a digitization rate of 500 Hz, with a bandpass filter of 0.01–100 Hz. Electrode impedances will be kept below 5 kΩ and EOG will be recorded from two additional bipolar channels. EEG data will be segmented into 1.5–3 s epochs centered on subject's responses (at least 50 epochs) using EEGlab.

### Sample Size Calculation

For the sample size calculation, we assume an effect size(d) of 0.66 [upper limit for the 95% CI of the pooled effect size of tDCS on MDD (22) that for a two-side α of 0.05 and a power of 80%, requires a total of 76 patients (38 per group). We increased the sample size by 15% to 45 per group to account for unexpected factors. This sample size will be adequate to detect this magnitude of effect.

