Transcranial direct current stimulation (tDCS) is a non-invasive method of brain stimulation that is capable of depolarizing or hyperpolarizing the neural membrane and as such, it has been used in people suffering from depression, by placing the anode (excitatory) over the left and the cathode (inhibitory) over the right DLPFC, or by placing the anode over the left DLPFC and the cathode over the right supra-orbital region.

For instance, in one study, 64 MDD patients were randomized to 15 sessions of 2 mA tDCS over 3 weeks, and tDCS was shown to be able to decreased MDD symptoms (20). However, in another study, not only active tDCS was superior to sham but also the combination of tDCS with sertraline was significantly more effective in reducing depressive symptoms than either treatment alone (21). Although tDCS *per se* showed promising results in treating MDD, the previous trial highlights that the effects of tDCS can be enhanced by combining it with other interventions. Overall, tDCS seems to decrease MDD symptoms by a pooled effect size of 0.36 (22). Moreover, according to a recent individual patient data meta-analysis, tDCS seems to be less effective in high-resistant patients, suggesting that tDCS may be a promising add-on therapy to therapies such as the cognitive behavioral therapy (CBT) (23) or cognitive control therapy (24, 25).

CBT is an empirically validated therapy for the treatment of MDD. Several studies have demonstrated the efficacy of CTB alone (26, 27) or as adjuvant to medication (28–30) in acute depression. Another advantage of CBT over anti-depressant drugs is its long-term effects, namely protecting against relapses and recurrences after active treatments has ended (27, 31, 32). Additionally, CBT is a well-established therapy that can restore or normalize abnormal brain activity, namely prefrontal alpha activity (33). Namely, an increase in left frontal brain activity after CBT in individuals with anxiety and depression.

It is important to highlight that MDD seems to induce profound changes in the brain, namely structural alterations in fronto-cingulate-striatal circuits (34–36). However, and somewhat surprisingly, first episode MDD patients have not been extensively studied with tDCS (37, 38). These first episode MDD patients provide an interesting opportunity, as their brains were not changed by the pharmacological treatments, by the time course, or by the recurrence of MDD episodes (and other comorbidities).

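### The trial is sized on the upper 95% confidence limit (d = 0.66) without a stated reason; at the same source's pooled effect of 0.36, power is about 34% to 39%, and the protocol does not say so

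*Protocol article*

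**What the plan says.** The Sample Size Calculation section takes its planning effect from a meta-analysis: "we assume an effect size(d) of 0.66 [upper limit for the 95% CI of the pooled effect size of tDCS on MDD (22". With that input it states that the trial "requires a total of 76 patients (38 per group", using two-sided α of 0.05 and 80% power. It then adds a margin: "We increased the sample size by 15% to 45 per group to account for unexpected factors". The section closes: "This sample size will be adequate to detect this magnitude of effect".

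The Background cites the same reference for the average effect: "Overall, tDCS seems to decrease MDD symptoms by a pooled effect size of 0.36 (22". The value 0.36 does not appear in the Sample Size Calculation section, and no power is given for it.

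The Statistical Analysis section (Primary Outcome) plans a mixed-model ANOVA of MADRS with intervention and time as factors. Baseline is not among the listed time points. Covariates, severity among them, enter only if the groups differ significantly at baseline.

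**The concern.** The planning value is 0.66/0.36 = 1.83 times the only central estimate of the tDCS effect in the document, and both values come from one reference. The section on sample size gives no reason for planning on the upper limit rather than on the pooled value or something between. The stated power therefore describes only the favourable end of the cited interval.

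If the true effect of active over sham tDCS on a CBT background is near 0.36, the trial is more likely to miss it than to find it. A reader who sees 80% power and a sentence on adequacy could then take a non-significant result as stronger evidence against tDCS than it would be. The stakes are how the trial's sensitivity is presented and whether the planned analysis uses the precision already available in the data.

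**Working it through.** **Inputs.** Planning effect 0.66, two-sided α 0.05, power 80%, 38 then 45 per arm (Sample Size Calculation). Pooled effect 0.36 (Background). Allocation 1:1 (Randomization). Both arms receive CBT, so the contrast is active versus sham tDCS.

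**Method.** Two-sample t-test with n per arm: noncentrality d × √(n/2), 2n − 2 degrees of freedom, two-sided 5% critical value. This approximates the planned mixed model; the documents give no within-patient correlations with which to do better.

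**Step 1: reproduce the plan.**
- Solving for 80% power at d = 0.66 gives n = 37.02, rounded up to 38 per arm, 76 in total. This agrees.
- 38/(1 − 0.15) = 44.7, rounded up to 45 per arm. This agrees.
- Power at 0.66 is 81.0% with 38 per arm and 87.2% with 45.

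**Step 2: power at the pooled effect.**

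| Per arm | Noncentrality at d = 0.36 | Critical t | Power at 0.36 | Effect detectable with 80% power |
|---|---|---|---|---|
| 38 | 0.36 × √19 = 1.569 | 1.993 | 34.1% | 0.65 |
| 45 | 0.36 × √22.5 = 1.708 | 1.987 | 39.3% | 0.60 |

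The normal approximation gives 34.8% and 40.0%. For scale, 80% power at 0.36 would need 122.1, so 123 per arm before any inflation, or 123/0.85 = 144.7, so 145 per arm with the plan's 15% margin. The second figure is the one to compare with 45.

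**Step 3: what baseline adjustment would recover.** With baseline-outcome correlation r, adjustment shrinks the residual SD by √(1 − r²), so the effective standardized effect is 0.36/√(1 − r²). This reads d as scaled by the unadjusted SD. The documents give no r, so three values are assumed.

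| Assumed r | Effective d | Power, 38 per arm | Power, 45 per arm |
|---|---|---|---|
| 0.3 | 0.377 | 36.8% | 42.5% |
| 0.5 | 0.416 | 43.2% | 49.6% |
| 0.7 | 0.504 | 58.3% | 65.7% |

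Power stays below 80% throughout this range.

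**The case against.** The strongest defence is that nothing stated is false. The protocol says openly that 0.66 is an upper limit, its arithmetic reproduces, and its closing sentence is tied to that magnitude of effect. All of this stands. A reader might infer that the 80% figure is wrong; it is not, because it is correct for the input given. What is missing is the consequence of that input at 0.36.

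A second defence is that a larger effect is argued for. The Abstract, Background and Discussion say that tDCS does better alongside other treatment, citing a trial with sertraline. The Background and Discussion say that it is less effective in highly resistant patients, whereas this sample is drug-naïve and first-episode. The section on aims hypothesises synergy. So it would be wrong to say that the protocol gives no argument. These points bear on whether 0.36 is the right central value here, and the protocol never calls 0.36 its best estimate for tDCS added to CBT. But the argument is qualitative: no effect size is offered for this combination, and the sample size section does not invoke it.

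A third defence is that the planned mixed model may be more precise than a t-test. That is possible, so the t-test figures are approximate. But the listed time points omit baseline, and covariate entry depends on a significance test, so a gain from baseline adjustment is not secured.

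**Conclusion.** The point holds as one of undisclosed sensitivity to an optimistic input whose choice is not explained. At the pooled effect that the protocol itself quotes, power is about 34% with 38 per arm and 39% with 45, against 81% and 87% at the planning value. These figures rest on an unadjusted two-sided 5% t-test, and the range runs from the 76 patients of the calculation to all 90 randomized.

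A reader might go further and infer that 0.66 is improbable, or reconstruct a lower limit by reflecting the interval around 0.36 and average the power over it. The documents do not support this. They give only the centre and the upper limit, symmetry would be an assumption, and an interval for a mean across studies is not a distribution for the effect in this population and combination. Nor do they support a claim that admitting mild cases (MADRS 7 and above) lowers power: power here depends on the standardized effect, and no SD or severity distribution is given.

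This should be fixed. It is not critical, because the input is disclosed and the calculation is correct.

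**What to change.** Keep 90 patients and make two changes.

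1. In the Sample Size Calculation section, give the reason for planning on 0.66 and state power at both values. For example: with 76 to 90 evaluable patients, power is 81% to 87% at d = 0.66 and 34% to 39% at the pooled estimate of 0.36 (unadjusted t-test); the effect detectable with 80% power is 0.65 to 0.60. Qualify the adequacy sentence, without deleting it, so that it is clear the trial is not adequately powered for the pooled estimate.

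2. In the Statistical Analysis section (Primary Outcome), replace the rule that covariates enter only on significant baseline differences with mandatory adjustment for baseline MADRS. The trial already collects this score before the intervention.

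The cost is wording and a pre-specified covariate, with no added patients or visits. The trial is still recruiting, according to its status section. The drawback is that the stated power looks less favourable, and adjustment narrows the shortfall at 0.36 without closing it.
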